### Random allocation

2.3

Before starting the study, a randomization list is produced using software-generated randomized numbers; the randomization depends on random blocks of 10. Eligible participants are divided into 3 groups according to completely randomized design: combined group (music therapy + Tai Chi), music therapy alone group and Tai Chi alone group (Fig. 1). The program duration is 12 months. Participants are enrolled by the research assistant. After baseline examination, all patients will be given a full explanation of the treatment protocol and will be required to sign a written informed consent for study participation and for the publication of the results. All the data collectors, statistical analysts, as well as result assessors are not aware of grouping assignment (Fig. 1).

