### Statistical analysis

2.6

The analyses will be performed using SPSS 22.0.0 (SPSS Inc, Chicago, IL). Frequencies and descriptive statistics will be used for patients’ demographic presentation, while means and standard deviations will be calculated for the continuous variables and group differences will be analyzed by using Pearson *χ*^2^test for categorical variables. Kolmogorov–Smirnov test will be applied to check the distribution of data. Independent *t* test will be used in case of normally distributed data, whereas Mann–Whitney *U* test for non-normal distributions. *P* < .05 will be considered significant for all analyses.

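### Blocks of 10 cannot hold three arms in equal numbers, and the same section also calls the allocation completely randomised

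*Protocol article*

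**What the plan says.** The section on random allocation (2.3) of the protocol article describes a list made before the study starts: "a randomization list is produced using software-generated randomized numbers". It adds that "the randomization depends on random blocks of 10". The next sentence reads "Eligible participants are divided into 3 groups according to completely randomized design", and the arms are "combined group (music therapy + Tai Chi), music therapy alone group and Tai Chi alone group". The methods part of the abstract repeats the description of the design but does not mention blocks.

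The article states no allocation ratio, no second block size, no rule for the place left over in each block, and no total or per-arm sample size.

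**The concern.** Two things do not fit together.

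- **Block size and number of arms.** Permuted blocks are used so that the arms meet their target ratio at the end of every block. With three arms and no ratio given, a reader will take the target to be 1:1:1, and a block of 10 cannot meet it.
- **Blocking and the named design.** A blocked list is restricted randomisation: the counts in each block are fixed in advance. A completely randomised design, in its usual sense, is unrestricted: each assignment is drawn without regard to earlier ones. Adjacent sentences give both descriptions for one list.

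What is at stake is mainly whether the allocation can be reproduced and audited. From this text, one programmer could build a list with a fixed 4:3:3 split, another could vary the arm that gets the extra place, and a third could use simple randomisation. The text does not say which is meant.

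**Working it through.** **Inputs.** The block size of 10 and the three arms come from section 2.3. The article has no sample size, so totals of N = 30, 90 and 150 are assumptions that show a range. Equal allocation is also an assumption. There is no stated figure to reproduce.

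**Step 1: divisibility.** 10 = 3 × 3 + 1, so one place is left over and the most even split is 4/3/3. Ten does fit some unequal ratios exactly, such as 4:3:3, 2:2:1 (4/4/2) and 3:1:1 (6/2/2). None is stated. Equal allocation needs blocks of 3, 6, 9, 12 and so on.

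**Step 2: the extra place always goes to the same arm.** After k = N/10 blocks the arms hold 4k, 3k and 3k:

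| Assumed N | Arms | Equal allocation |
|---|---|---|
| 30 | 12/9/9 | 10/10/10 |
| 90 | 36/27/27 | 30/30/30 |
| 150 | 60/45/45 | 50/50/50 |

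With a common outcome variance, the variance of a difference between two means is proportional to 1/n1 + 1/n2. Per block of 10:

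- equal allocation: 2/(10/3) = 0.600
- the two smaller arms: 1/3 + 1/3 = 0.667, ratio 0.667/0.600 = 1.11
- the larger arm against a smaller one: 1/4 + 1/3 = 0.583, ratio 0.583/0.600 = 0.97

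These ratios do not depend on N.

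**Step 3: the extra place goes to a randomly chosen arm in each block.** For N = 30 there are 3 blocks and 3³ = 27 equally likely outcomes. In 6 the arms are equal (difference 0), in 18 the largest and smallest arms differ by 2, and in 3 they differ by 3. The mean difference is (6 × 0 + 18 × 2 + 3 × 3)/27 = 45/27 = 1.67, and the arms are exactly equal in 6/27 = 22% of lists. For N = 90 the chance of exact equality is 9!/(3!)³/3⁹ = 1680/19683 = 8.5%. The other figures below come from a simulation of 20,000 lists per setting.

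| Assumed N | Mean largest minus smallest arm, blocks of 10 with random extra place | Same, simple randomisation |
|---|---|---|
| 30 | 1.7 | 5.3 |
| 90 | 2.9 | 9.2 |
| 150 | 3.8 | 12.1 |

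The last column shows that the two descriptions in section 2.3 are different procedures: at each N, simple randomisation leaves a mean difference about three times as large.

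**Step 4: the extra place rotates over the arms.** Three blocks give each arm 4 + 3 + 3 = 10 places, so balance returns every 30 participants. The article describes no such rotation.

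**The case against.** The strongest reply is that equal allocation is never stated. A planned 4:3:3 or 2:2:1 ratio would fit a block of 10 exactly. The flow diagram cited for the allocation is not shown, and a full protocol could give the ratio. This stands as a limit: the block size is wrong only if 1:1:1 is meant. It does not remove the point, because the article fixes a block size that does not fit the natural reading of three arms with no ratio, and nothing in the visible text settles it.

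A second reply is that completely randomised may be loose wording for a parallel, unstratified design. That is possible. The words as printed still conflict with blocking, and the abstract carries them without any mention of blocks.

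Stronger readings are tempting, and three of them should be set aside.

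- **That the trial cannot be balanced.** The arithmetic applies to each block. Rotation balances the arms every 30 participants, and a random extra place keeps them close.
- **That precision falls by 11% throughout.** That figure applies to one contrast, and only if the same arm always takes the extra place. The trial's stated question is combined therapy against each treatment alone. If the combined arm took the extra place, both of those contrasts would have about 3% less variance. If a single-therapy arm took it, one would have about 11% more and the other about 3% less.
- **That the enrolling research assistant can guess assignments, so selection is biased.** A single fixed block size is a recognised weakness, and the treatments are visible to those who deliver and receive them. But the article does not say that the assistant sees earlier assignments, knows the make-up of a block or holds the list. Nor is 10 an unusually guessable size. If the composition is known, the expected number of fully determined places in a 4/3/3 block is 1 + 24/90 + 36/720 + 24/5040 = 1.32 of 10, or 13%. In a 3/3/3 block of 9 it is 1 + 2/8 + (2/8)(1/7) = 1.29 of 9, or 14%. Guessability is a reason to vary and conceal block sizes, not a demonstrated harm.

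**Conclusion.** The point holds in a limited form. As written, the block size does not fit three equal arms, and the named design does not fit a blocked list. These are faults in what the text states, not details left to a fuller document.

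The size is modest. It rests on two assumptions: that 1:1:1 is intended, and, for the arm counts, that N lies between 30 and 150. The worst case is a consistent 4:3:3 split, which costs one contrast about 11% in variance and gains the other two about 3%. Unequal arm sizes of this order do not bias the planned tests. The main cost is an allocation procedure that cannot be reproduced or audited from the text. Severity is moderate: worth correcting before the list is used, but no planned comparison is invalid because of it.

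**What to change.** 1. State the allocation ratio in section 2.3.
2. If it is 1:1:1, use permuted blocks whose sizes are multiples of three, preferably varied at random and not disclosed to those who enrol, for example 6 and 9. Completed blocks then split 2/2/2 or 3/3/3. If an unequal ratio is intended, give it and confirm that the block size fits.
3. In section 2.3 and in the abstract, replace the description as completely randomised with one that matches the blocked list, such as a parallel-group design with permuted-block randomisation.
4. If the list is already in use, report how it was actually built, including how the tenth place in each block was assigned.

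Before enrolment this costs about two sentences and a regenerated list. After enrolment has begun it costs only an accurate description.

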### Study population

2.2

Participants recruited into the study need to fulfill the following criteria: aged 18 to 70 years; residing in the targeted communities for at least 1 year; mentally adequately alert to complete the intervention as judged by trained researchers; with a GDS score of 11 to 25 (inclusive of 11 and 25), and agreeable to take part in entire intervention process. Participants with the following characteristics are excluded: individuals who are bedridden, or with severe hearing or visual impairment leading to difficulty completing the intervention; those with a stroke or cardiovascular event within the past 6 months and the presence of other conditions which require medical assessments prior to physical exercise; individuals with a GDS score of 26 or greater (severely depressed); those who are receiving medical treatment for depression; those who exercise more than 3 times per week.

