### Intervention and control protocols

2.4

The music therapy group is provided by a trained music therapist, who is registered with the appropriate professional association or registration body in his or her country and should also be skilled as a musician. To facilitate individual relationship-building, the music therapist will offer each resident an initial 20 minutes assessment with the aim of determining their musical preferences and starting to build individual rapport. The music therapist will also use other sources to determine the participants’ musical biography, cultural background, history, personal strengths, resources and disabilities, and any other information that could be useful to bring into music therapy sessions.

Tai Chi is taught as a 24-form Yang style; instruction is given 5 days per week for 1 h for 12 weeks. The Tai Chi group is led by an experienced practitioner who will demonstrate a set of slow, nonstrenuous movements coordinated with deep breathing. Participants are taught traditional Sun and Yang styles of Tai Chi. Instructors will take participants through warm-up exercises for 5 minutes, Tai Chi movements and form for 20 minutes and cool down exercises for 5 minutes. At the end of the 12-week period, participants are encouraged to continue Tai Chi, either alone or via a community group; however, no assistance is provided by the investigators during this period.

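### A single published block length of 10 makes upcoming allocations partly predictable if whoever enrols or judges eligibility sees earlier assignments

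*Protocol article*

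**What the plan says.** The protocol article, section 2.3 (Random allocation), describes the list as follows: "Before starting the study, a randomization list is produced using software-generated randomized numbers", and "the randomization depends on random blocks of 10". One length is given, with no mention of variation. The next sentence describes the scheme differently: "Eligible participants are divided into 3 groups according to completely randomized design". The groups are "combined group (music therapy + Tai Chi), music therapy alone group and Tai Chi alone group". No allocation ratio is stated.

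On roles, section 2.3 says "Participants are enrolled by the research assistant" and, later, "All the data collectors, statistical analysts, as well as result assessors are not aware of grouping assignment". The enrolling role is not named in that second sentence.

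Section 2.2 (Study population) makes one entry criterion a judgement: "mentally adequately alert to complete the intervention as judged by trained researchers". Section 2.4 shows that the arms are different activities, for example "The Tai Chi group is led by an experienced practitioner who will demonstrate a set of slow, nonstrenuous movements", whereas music therapy is delivered by a music therapist. The conclusion of the abstract says that the sample comes from one health centre.

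**The concern.** With blocks of one known length, anyone who can see the assignments made so far in a block knows something about those still to come, and near the end of a block may know them outright. Three features make this worth attention here. The length is published. The centre is single, so a block is not spread over sites. And the instructors and participants necessarily know which activity is being given.

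Eligibility is partly a judgement, and the timing of enrolment is in someone's hands. If either were influenced by the arm expected next, the people entering the three arms could differ systematically. Adjustment for measured baseline variables would not fully repair that.

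The point does not depend on 10 failing to divide by three. A fixed block of 9 whose length is known is about as predictable.

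**Working it through.** **Inputs.** From section 2.3: block length 10, three arms. Assumed, because the article gives no ratio: the nearest-to-equal split, 4/3/3. Two cases are taken, (a) the favoured arm is the same each time and known to the guesser, and (b) it is random and unknown. In both, the guesser sees all earlier assignments in the block, knows where the block starts, and names the most likely next arm. The document has no predictability figure to reproduce. 10/3 is not a whole number, so an equal split within a block is impossible.

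**Correct guesses.** Let c be the places left for each arm and n their total. The expected number of correct guesses satisfies

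G(c) = max(c)/n + Σ (c_i/n) · G(c with one place of arm i removed), G(0) = 0.

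- (a) Solved exactly from c = (4, 3, 3): G = 151/28 = 5.39 of 10, or 53.9%.
- (b) The same recursion, averaging over which arm holds the fourth place given the assignments seen: 34/7 = 4.86 of 10, or 48.6%.
- Simple randomisation: 1/3 = 33.3%.

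The excess is 48.6 − 33.3 = 15.3 to 53.9 − 33.3 = 20.6 percentage points.

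**Places known with certainty.** The expected closing run of an arm with n_i places in a block of N is n_i/(N − n_i + 1).

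- (a) 4/7 + 3/8 + 3/8 = 1.32 of 10 (13.2%).
- (b) The guesser is certain only once the favoured arm has shown its fourth place and one of the other arms is used up: 3/8 + 3/8 = 0.75 of 10 (7.5%).

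**Places where at least one arm can be ruled out.** The expected number of places after the last one of arm i is (N − n_i)/(n_i + 1).

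- (a) By inclusion and exclusion: 6/5 + 7/4 + 7/4 − 1.32 = 3.38 of 10.
- (b) Only after the favoured arm's fourth place: 6/5 = 1.2 of 10.

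**Alternatives.**

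| Scheme | Correct guesses | Certain places |
|---|---|---|
| Simple randomisation | 33.3% | 0% |
| Fixed 10, case (b) | 48.6% | 7.5% |
| Fixed 10, case (a) | 53.9% | 13.2% |
| Fixed 9, length known | 53.2% | 14.3% |
| Fixed 12, length known | 51.2% | 11.1% |
| Fixed 15, length known | 49.7% | 9.1% |
| Random mix of 6, 9, 12, undisclosed | about 52.6% | about 2% |

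The last row is simulated over 90 allocations. The guess rate there comes from always naming the least-used arm. A stricter simulation, in which the guesser knows the set of lengths but not their order and updates optimally, gave 53.0% correct and 2.5% certain. For a mix of 9, 12 and 15 it gave 50.5% and 1.9%. Varying the lengths therefore removes most of the certainty but hardly moves the average guess rate, which in case (b) would even be slightly higher than now.

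**The case against.** A reader might infer that this is an open-label trial in which the enrolling assistant watches allocations accumulate, guesses the next arm and steers people accordingly. The article does not support that.

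- It never uses the term open-label. That participants and instructors cannot be masked is a safe inference from section 2.4, but nothing says that recruiting staff see past assignments.
- The assistant is simply not named among the unaware, and may be one of the data collectors who are.
- The alertness judgement belongs to trained researchers, who are not said to include the assistant. It concerns mental alertness. Physical limits are handled by separate exclusions in section 2.2.
- Who holds the list and how assignments are released are not described. A condensed article commonly leaves this to the full protocol, so the silence is not a defect.
- The design is also called completely randomised. Taken literally, that means no blocks and no advantage to a guesser.
- Even in case (a), about 87% of places are not certain, and in case (b) about 92%.

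All of this stands, and it makes the risk conditional. What remains is what the article does fix: one published block length on a list made in advance, and a statement of who is unaware that does not name the enrolling role. Certainty is not needed for selection bias, since guessing better than chance is enough.

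**Conclusion.** The point holds conditionally. Under the stated blocks of 10, someone who sees earlier assignments and can place the block boundaries would guess the next arm correctly about 49% to 54% of the time instead of 33%, and would be certain of about 0.75 to 1.3 places in every 10.

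This rests on an assumed 4/3/3 split and on access to past assignments that the article neither states nor rules out. If complete randomisation is the scheme actually used, the advantage is nil. The two descriptions in section 2.3 contradict each other and must be reconciled in any case. The documents do not show that enrolment has been or will be steered. This is an inexpensive improvement to a stated rule, not a demonstrated bias.

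**What to change.** In section 2.3:

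1. State one scheme, either blocks or complete randomisation, and the allocation ratio.
2. If blocks are kept, replace the fixed length of 10 with randomly varying lengths that are multiples of three, for example 6, 9 and 12, or 9, 12 and 15. Do not disclose the lengths to enrolling staff.
3. Add the enrolling assistant and the researchers who judge eligibility to those unaware of allocation, covering both past and upcoming assignments.
4. State that each assignment is released only after eligibility (including the alertness judgement), consent and baseline are recorded. If the full protocol already says so, one confirming sentence is enough.

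Items 3 and 4 are the main safeguard, because they take away the information on which guessing depends. Item 2 lowers the certain places from about 13% (7.5% in the less favourable case) to about 2%, and should not be presented as more than that.

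The cost is a re-generated list, which is needed anyway if an equal split is intended, since 10 does not divide by three. Balance at any one moment is slightly looser than with a short fixed block: two arms can differ by up to 12/3 = 4 participants within a block of 12, or 15/3 = 5 within a block of 15, against 9/3 = 3 within a block of 9. The gap closes at each block end. With 4/3/3 blocks it does not, and if the same arm is always favoured it grows by one per block.

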**Figure 1 F1:**
[figure not shown]
Consolidated standards of reporting trials (CONSORT) diagram of patient flow through the study.

### Intervention and control protocols

2.4

The music therapy group is provided by a trained music therapist, who is registered with the appropriate professional association or registration body in his or her country and should also be skilled as a musician. To facilitate individual relationship-building, the music therapist will offer each resident an initial 20 minutes assessment with the aim of determining their musical preferences and starting to build individual rapport. The music therapist will also use other sources to determine the participants’ musical biography, cultural background, history, personal strengths, resources and disabilities, and any other information that could be useful to bring into music therapy sessions.

Tai Chi is taught as a 24-form Yang style; instruction is given 5 days per week for 1 h for 12 weeks. The Tai Chi group is led by an experienced practitioner who will demonstrate a set of slow, nonstrenuous movements coordinated with deep breathing. Participants are taught traditional Sun and Yang styles of Tai Chi. Instructors will take participants through warm-up exercises for 5 minutes, Tai Chi movements and form for 20 minutes and cool down exercises for 5 minutes. At the end of the 12-week period, participants are encouraged to continue Tai Chi, either alone or via a community group; however, no assistance is provided by the investigators during this period.

### Outcomes

2.5

Questions on the patients’ sociodemographic characteristics concerned their age, sex, marital status, level of education, and occupation type (Table 1). Quality of life is measured using the Chinese version of the WHOQOL-BREF questionnaire. The WHOQOL-BREF consists of 26 items, scored on a 5-point Likert scale of 1 to 5, with an item score of 1 indicating “not at all” or “very poor/dissatisfied” and an item score of 5 indicating “very good,” “completely,” or “extremely.” There are 2 general items regarding health conditions which would be analyzed independently. The other items evaluate quality of life (QOL) in 4 main domains: physical health (7 items), psychological (6 items), social relationships (3 items), and environment (8 items). Three items are phased negatively and hence, scored in reverse. The domain scores are computed separately and the raw score of each domain is converted into a 0 to 100 transformed score, according to the WHOQOL user manual. After conversion, the maximal scores for the physical health, psychological, social relationships, and environment domains are 100 respectively, with a higher score indicating a better QOL. Satisfactory reliability and validity of WHOQOL-BREF have been demonstrated in the Chinese population with a Cronbach-a coefficient of 0.892.

**Table 1 T1:** Patient baseline demographics.

Demographics	Combined group	Music group	Tai Chi group	*P* value
Number of patients				
Age^∗^ (y)				
Male sex (no. [%])				
BMI^∗^ (kg/m^2^)				
Follow-up^∗^ (mo)				

BMI = body mass index.

∗ The values are given as the mean and the SD.

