However, it is still controversial whether combined music and Tai Chi therapy will be more effective than treatment alone for patients with major depression.^[10]^ Based on the separate effectiveness of Tai Chi and music mentioned above, we combined Tai Chi with soft relaxing Chinese folk music to determine whether a synergistic effect would be present in the control of depressive symptoms among community-dwelling persons in China. Therefore, the primary objective of the present study was to evaluate the efficacy of Tai Chi and music therapy on psychological status and quality of life among patients with major depressive disorder in China.

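### The trial aims to test synergy on depressive symptoms, but Section 2.5 names only a quality-of-life instrument and the one depression scale is used for eligibility alone

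*Protocol article*

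**What the plan says.** **Aim.** The Introduction, repeated in the Discussion, says the two therapies are combined "to determine whether a synergistic effect would be present in the control of depressive symptoms among community-dwelling persons in China". The next sentence gives the primary objective, which is to "evaluate the efficacy of Tai Chi and music therapy on psychological status and quality of life among patients with major depressive disorder in China".

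**Depression scale.** Section 2.2 (Study population) admits people "with a GDS score of 11 to 25 (inclusive of 11 and 25") and excludes "individuals with a GDS score of 26 or greater (severely depressed"). The GDS is mentioned nowhere else.

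**Outcomes.** Section 2.5 covers sociodemographic questions and one instrument: "Quality of life is measured using the Chinese version of the WHOQOL-BREF questionnaire". It describes this tool at length: two general items handled on their own, and then "The other items evaluate quality of life (QOL) in 4 main domains: physical health (7 items), psychological (6 items"). Of the two remaining domains, environment has 8 items and social relationships has 3. Each domain is rescaled to run from 0 to 100.

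**Analysis.** Section 2.6 (Statistical analysis) names tests and a significance level but no outcome variable.

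**The concern.** The trial enrols people by their level of depressive symptoms and justifies the combined arm by its hoped-for effect on those symptoms. Its outcome list then contains no depression score. A team following the article to the letter would know each participant's GDS at entry and nothing about it afterwards.

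The loss could not be repaired later. A missing test or model can be added at the analysis stage, but a post-treatment score that was never collected cannot be recovered. Any statement about depressive symptoms would have to be inferred from quality-of-life scores, which the article does not present as measuring them.

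**Working it through.** The point involves no sample size, power or error rate, so the check compares what the article wants to learn with what it says it will measure after baseline.

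| What the trial wants to learn | Where stated | Measure named in Section 2.5 |
|---|---|---|
| Synergy in controlling depressive symptoms | Introduction; Discussion | None |
| Effect on psychological status | Primary objective (Abstract, Introduction, Discussion) | None assigned; the 6-item WHOQOL-BREF psychological domain is the nearest |
| Effect on quality of life | Primary objective (same places) | WHOQOL-BREF |

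**Step 1: find every depression measure.** There is one, the GDS. Section 2.2 uses it twice, as an entry range (11 to 25) and as an exclusion (26 or greater). Both uses come before randomisation. Depression instruments listed as outcomes: 0 of 1.

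**Step 2: check whether the WHOQOL-BREF description leaves room for another instrument.** The items are 2 general + 7 physical + 6 psychological + 3 social + 8 environment = 26, which matches the stated 26. The description accounts for every item, so no depression scale is hidden within it.

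**Step 3: look for a depression score elsewhere.**
- Section 2.6 names no outcome.
- Table 1 has rows for number of patients, age, sex, body mass index and length of follow-up. It has no GDS row.
- Section 2.1 (Ethical approval) mentions a questionnaire taken before the sessions without giving its content. Given before treatment, it could not supply a post-treatment score.
- Figure 1 is not available here. Its caption describes patient flow only.

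**Step 4: ask what the psychological domain can carry.** Section 2.5 places its six items among those that evaluate quality of life. The article does not assign the domain to the psychological-status objective and does not call it a measure of depression severity. It may speak in part to psychological status. It does not fill the first row of the table.

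**The case against.** **An article condenses the full protocol.** Ordinarily this is a good answer, and it disposes of complaints about visit schedules and ranking of outcomes taken alone. It does not dispose of this point. Section 2.5 gives item counts, reverse scoring, rescaling and a reliability coefficient for the quality-of-life tool. A section that detailed, with no measure for the stated target, shows a mismatch between aim and outcome.

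**The formal objective does not mention depressive symptoms.** This is correct, and it limits the point. Depressive symptoms appear in the rationale sentence just before the objective. The objective itself names psychological status and quality of life; the second is measured directly and the first has a partial proxy. A reader might infer that the plan cannot answer its main question at all. The document does not support that.

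**The headline result could be chosen from many.** A reader might count six WHOQOL-BREF scores (four domains plus two general items) at 12 weeks and at 12 months and arrive at 6 × 2 = 12 candidate main results per comparison. The article does not support that count. Twelve weeks is the Tai Chi instruction period in Section 2.4 and 12 months is the programme duration in Section 2.3 ("The program duration is 12 months"). Neither is stated to be an outcome visit, and the two can coexist, because Section 2.4 describes unassisted continuation after instruction ends.

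**The GDS may not be the right scale.** This stands as a caution. The article neither expands the abbreviation nor reports its validity, and it enrols adults aged 18 to 70. If the G stands for geriatric, which is an assumption, suitability for younger participants needs justification.

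**Conclusion.** The concern holds for the depressive-symptom aim. As written, the trial has no post-baseline measure of depressive symptoms, so its synergy question on those symptoms could not be answered. The quality-of-life part of the objective is unaffected. Psychological status is covered at most in part, by one 6-item domain.

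This rests on reading Section 2.5 as the complete list of outcome instruments, which its level of detail supports. A fuller protocol that repeats the GDS would remove the practical harm, though the article would still need correcting.

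The mismatch should be settled before follow-up data are collected. A depression score is necessary for the synergy question. Whether three active arms are enough to identify synergy is a separate matter, not judged here.

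**What to change.** In Section 2.5, do one of the following.

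1. **Add a depression-severity score as a named outcome.** The simplest choice is the GDS already given at screening, repeated after baseline at one fixed time that is the same for all three arms. That time should be defined for every arm, because the 12-week period in Section 2.4 is stated only for Tai Chi and no duration is given for music therapy. State whether this score or a named WHOQOL-BREF domain is primary. The sponsor should confirm that the scale suits the enrolled age range of 18 to 70 years, or name another depression scale that does.

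2. **If no depression measure will be repeated,** restrict the stated aim and the eventual conclusions to quality of life, and remove the claim to test synergy on depressive symptoms from the Introduction and Discussion.

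The first option costs a change of wording and one additional short questionnaire at follow-up. Participant burden should be small if it is given together with the WHOQOL-BREF; the article shows no visit schedule, so this cannot be confirmed from it. The second option costs nothing to run but gives up the question that motivated the combined arm.
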